### Enrolment procedure

One to two study team members (henceforth referred to as data collectors) are placed full-time at each of the participating healthcare facilities for the duration of the enrolment period. The ART nurse at each of the participating healthcare facilities referes all ART patients who live in the facility’s catchment area to the data collector. The data collector introduces the study to the patient, and, provided the patient gives initial verbal consent, ascertains whether the patient is 1) stable on ART (see eligibility criteria), and 2) lives in the facility’s catchment area. If both criteria are fulfilled, the data collector conducts the written informed consent procedure, administers a tablet-based baseline questionnaire, and measures the participant’s height and weight. Next, the data collector asks the community outreach nurse at the facility to take a blood sample, which is sent for a measurement of blood hemoglobin. In addition, the blood sample is sent for an HIV viral load in participants who have not had a viral load measurement in the 12 months prior to study enrolment. Lastly, the data collector takes a map cue (a description of the location of the participant’s residence) from the participant and records his/her mobile phone number as well as the mobile phone number from at least one household member. These details are then passed to the CHW assigned to the neighborhood, in which the participant lives.

### Description of the interventions

#### Home delivery of ART

In clusters randomized to ART home delivery, a CHW visits participants at home to provide counseling (see below), deliver a supply of ART, and perform an ART pill count. After a year on ART, most patients in Dar es Salaam are scheduled to attend the facility every two months. We maintain a participant’s usual facility ART schedule in the ART home-delivery intervention. For instance, an ART patient who was scheduled to visit the facility every two months (and was provided with a two-months ART supply) receives a CHW visit for ART home delivery every two months (and receives a two-months ART supply from the CHW). The CHWs received three days of training in the home delivery of ART and in counseling skills for this intervention prior to the start of the trial.

#### Nutrition counseling

CHWs provide counseling to all participants in both the intervention and control arms during their home visits. As described in the study design section, half of the clusters in each the intervention and control arm of the trial were randomized to standard counseling, and half to standard plus nutrition counseling. The standard counseling covers family planning, ART adherence, and prevention of HIV transmission. Nutrition counseling covers advice on 1) food production for those with access to a garden or plot of land, 2) a healthy diet for people living with HIV, 3) exercise, and 4) monitoring one’s weight. In addition, participants enrolled in the trial at one of the healthcare facilities randomized to the nutrition counseling intervention receive a pack of seeds (amaranth, cowpea, or pumpkin) at enrolment if they report to have access to a garden or plot of land where they can grow vegetables for their own consumption.

### Endpoints

The primary endpoint for the ART home delivery intervention is the proportion of enrolled patients with a suppressed HIV viral load at the end of the study period (i.e., when the study exit assessment is performed). A substantial proportion of participants does not have a recent viral load or CD4-cell count at enrolment. As described above, the study team obtains a blood sample from these patients at enrolment and sends it to the public healthcare system’s laboratory for a viral load measurement. Because the delay in receiving the viral load count from the laboratory varies between participants (and thus, the time point at which eligibility for ART home delivery can be assessed at intervention facilities), the length of time for which intervention participants receive ART at home varies between participants at a healthcare facility. Participants in the ART home-delivery intervention receive ART at home for a period varying between one and 11 months, and for an average of six months.

The primary endpoint for the nutrition counseling intervention is the mean BMI of participants who received standard counseling by CHWs versus those who received standard plus nutrition counseling, assessed at the end of the study period. Secondary endpoints of this trial (all assessed at the end of the study period) are: 1) participants’ healthcare expenditures in the last six months, 2) self-reported ART adherence during the last one month, 3) the proportion of patients with access to a plot of land who grow vegetables or fruits for their own consumption, 4) diversity of dietary intake, and 5) the proportion of participants who are anemic.

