### Sample size

Over the enrolment period, we expect to recruit approximately 700 participants in each of the two trial arms (1,400 participants in total). We calculated the design effect (taking into account clustering of outcomes at the facility-level and varying cluster sizes) for this trial using the ‘clustersampsi’ function in Stata [31]. The design effect was then used to adjust the expected power calculated for a non-inferiority trial under individual randomization, which we determined using the ‘ssi’ function in Stata [32]. Our calculations assumed that 85% of enrolled participants are virally suppressed at baseline as found in a recent cross-sectional study in Dar es Salaam [33]. The margin of non-inferiority was set at nine percentage points. We used a range of intra-cluster correlation coefficients (ICCs) from 0.005 to 0.020. Barnhart et al. calculated ICC values for CD4-cell count measures in Dar es Salaam [34]. The 6-months cumulative incidence for non-adherence to ART (defined as a 50% drop in CD4-count from its peak value and return to pre-ART CD4-count or lower after 168 days on ART or a viral load greater than 10,000 after 168 days on ART) had an ICC value of 0.016 (95% confidence interval: 0.009 to 0.029). We set the probability of a type one statistical error at 0.05 and assumed a correlation coefficient between baseline and endline viral load measurement of 0.5. We find that we are well powered (≥80% power) to detect modest one-sided differences (<9 percentage points) in the proportion of participants who are virally suppressed between the two study arms. Regarding the effect of nutrition counseling on BMI, we are well powered (≥80%) to detect a difference in mean BMI of approximately 1.0 kg/m^2^ or more between the participants in the standard versus the standard plus nutrition counseling arm. This difference is considerably smaller than the difference of 3.1 kg/m^2^ found by Alo et al. between female ART patients randomized to six months of nutrition counseling versus the standard of care in Southeast Nigeria [35]. The trial by Alo et al. is, to the best of our knowledge, the only randomized evaluation to date of the impact of nutrition counseling on BMI in ART patients.

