### Analysis plan

We will analyze the data by intention-to-treat analysis at the patient level in all primary analyses for this trial. The primary endpoint of this trial (i.e., the percentage of participants with a suppressed HIV viral load at the end of the study period) will be assessed by fitting robust clustered log-binomial models. Given the relatively small number of clusters in this trial, we cannot assume that randomization will eliminate confounding despite the matching of clusters described in the study design section. We will, therefore, adjust the analysis for viral load suppression at baseline. As viral load suppression is the outcome variable for the primary endpoint, adjusting for baseline viral load could be considered perfect adjustment for confounders. However, in secondary analyses, we will also adjust for other potentially confounding variables (e.g., participants’ socio-demographic characteristics) as a single baseline measurement may not account for trends in viral load suppression over time. Similarly, in secondary analyses, we will adjust for differing average exposure lengths to ART home delivery at each facility, and conduct subgroup analyses according to whether a participant received ART home delivery and by participants’ exposure length to ART home delivery.

Potential effect modification for any of the endpoints of this trial will be assessed through the likelihood ratio test. If statistically significant effect modification is present, we will present relevant results stratified by the effect modifier. All analyses will be conducted using Stata (Release 13; StataCorp, College Station, TX, USA).

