#### Consent

The data collectors placed at each of the study’s healthcare facilities will obtain written informed consent from all participants at enrolment into the study. To adhere to the intent-to-treat principle, patients who refuse to participate in the study at any time during the study period, including during enrolment, will be asked for consent to complete the study questionnaire, and to take a blood sample and BMI measurement at enrolment and at the end of the study period. The data collectors will also obtain written informed consent from respondents before administering the patient exit questionnaire and the healthcare provider questionnaire.

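### Exit BMI, the nutrition primary endpoint, has no stated adjustment for the baseline BMI that is collected, although the plan's reason for adjusting viral suppression applies to it equally

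*Protocol article*

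**What the plan says.** All references are to the protocol article.

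- **Endpoints.** The nutrition endpoint is a mean at one time point. Its definition opens with "The primary endpoint for the nutrition counseling intervention is the mean BMI of participants who received standard counseling by CHWs versus"; the other side of the contrast is the group given the nutrition package as well, and BMI is taken at study end. No change score, covariate or model is named.
- **Enrolment procedure.** The data collector "administers a tablet-based baseline questionnaire, and measures the participant’s height and weight", so baseline BMI is part of routine enrolment. The Consent section also asks people who decline participation for consent "to take a blood sample and BMI measurement at enrolment and at the end of the study period".
- **Analysis plan.** A model (log-binomial, clustered) is given for viral suppression. Because there are relatively few clusters, randomisation and matching are not trusted to remove all confounding, and the text continues: "We will, therefore, adjust the analysis for viral load suppression at baseline". BMI is not mentioned in that section. All primary analyses are to be by intention to treat.
- **Sample size.** A baseline–endline correlation of 0.5 is assumed for viral load. For BMI the section says only that "we are well powered (≥80%) to detect a difference in mean BMI of approximately 1.0 kg/m^2^ or more"; no SD, ICC or correlation specific to BMI is given.

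**The concern.** The trial has two randomised factors and a primary endpoint for each. Both factors are allocated over the same 48 facilities, 24 against 24. The argument that so few clusters can leave chance differences at baseline therefore carries over unchanged to counselling, but the remedy is written for one endpoint only.

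BMI is a natural candidate for baseline adjustment. It is measured in the same person at both ends of follow-up, and exit BMI depends heavily on starting BMI. If exit means are compared without it, facility differences in starting BMI stay in the estimate as noise. At stake are the precision of the nutrition result and its credibility if starting BMI happens to differ between packages.

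Table 1 makes such a chance difference a practical matter. The two very large hospitals in Temeke municipality (15,663 and 17,409 ART patients) were both allocated to nutrition counselling. Size matching could not prevent this. Within their home-delivery arms, the next largest Temeke facilities have 1,554 and 2,879 patients.

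**Working it through.** **Inputs from the article.** About 1,400 participants; 48 clusters; 24 against 24 for counselling; type I error 0.05; ICC range 0.005 to 0.020 (given in the viral-load calculation).

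**Assumptions, because the article gives no figure.** A 700/700 split by counselling package; a two-sided test; SD of BMI (5 kg/m² for illustration); CV of enrolled cluster size 0 to 1; baseline–exit correlation r of BMI. The same r is assumed to act within and between facilities.

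**Formulas**

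- Mean cluster size m = 1,400/48 = 29.17
- Design effect DE = 1 + ((1 + CV²)·m − 1)·ICC
- Detectable difference at 80% power = 2.80 × SD × √(2·DE/700)
- With baseline as covariate, SD is replaced by SD·√(1 − r²)

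**1. The plan's own figure.** A detectable difference of 1.0 kg/m² requires SD·√DE = 1/(2.80 × √(2/700)) = 6.68.

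- ICC 0.005, CV 0: DE = 1.14, so SD is at most 6.25.
- ICC 0.020, CV 1: DE = 2.15, so SD is at most 4.56.

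The stated figure is therefore plausible for an unadjusted comparison with an SD between about 4.6 and 6.3. It cannot be strictly reproduced. It also does not identify the analysis: SD 6, ICC 0.020 and r = 0.5 give 1.12 × 0.866 = 0.97 (CV 0) to 1.32 × 0.866 = 1.14 (CV 1), which fits about as well.

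**2. Effect of baseline adjustment.** Take SD 5, ICC 0.016 and CV 0.5. Then DE = 1 + (1.25 × 29.17 − 1) × 0.016 = 1.57, and the unadjusted difference is 2.80 × 5 × √(2 × 1.57/700) = 0.94.

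| r | variance removed (r²) | detectable difference, kg/m² | power for 0.5 kg/m² |
|---|---|---|---|
| none | 0% | 0.94 | 32% |
| 0.5 | 25% | 0.81 | 41% |
| 0.7 | 49% | 0.67 | 55% |
| 0.8 | 64% | 0.56 | 70% |
| 0.9 | 81% | 0.41 | 93% |

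More than half the variance is removed only when r exceeds √0.5 = 0.71.

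**3. Balance of the counselling allocation, from Table 1**

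| | nutrition | standard |
|---|---|---|
| clusters | 24 | 24 |
| CHWs | 186 | 173 |
| ART patients | 22,514 + 27,974 = 50,488 | 10,677 + 10,003 = 20,680 |
| ART patients without the two hospitals | 17,416 | 20,680 |

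Nutrition facilities hold 50,488/71,168 = 71% of ART volume, and the two hospitals account for the excess. Footnote b of Table 1 warns that these volumes are not the expected enrolment. Each of the two hospitals has only 3 CHWs.

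**The case against.** The strongest reply is that an end-of-study mean is a variable and a time point, not a model. A baseline-adjusted regression estimates exactly that contrast. The article gives no BMI model of either kind, and covariates for a second endpoint are often left to an analysis plan. This stands to the extent that a reader might infer a decision to ignore baseline BMI, and the article contains no such decision. It does not remove the point, because the article does set out baseline adjustment, with a reason, for one of two primary endpoints and does not extend it to the other.

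Four further inferences are tempting and are not supported:

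- **That most of the precision is given up.** This needs r above 0.71. The only correlation in the article, 0.5 for viral load, would remove 25% of the variance.
- **That the counselling groups are unequal in size.** The 71% share is ART volume, which footnote b separates from enrolment, while clusters and CHWs are near even. Baseline BMI would not correct unequal group sizes in any case.
- **That a null result would be uninformative.** A detectable difference of 1.0 implies a 95% interval half-width of about 1.96/2.80 = 0.7. Such a result would exclude the 3.1 kg/m² that the Sample size section cites from a nutrition-counselling trial in female ART patients.
- **That the word for receiving counselling in the endpoint definition signals an as-treated comparison.** The intention-to-treat sentence in the Analysis plan already governs all primary analyses.

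Chance differences between facilities are also random error, which the design effect allows for. They do not make the randomised comparison biased.

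**Conclusion.** The point holds as a gap in consistency and precision. Baseline BMI is collected, the plan's argument for adjustment covers it, and adjustment is written only for viral suppression. The randomised comparison remains valid without it, and the stated 1.0 kg/m² is plausible.

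The gain depends on quantities the article does not give. Under SD 5, ICC 0.016 and CV 0.5, the detectable difference moves from 0.94 kg/m² to between 0.81 (r = 0.5) and 0.41 (r = 0.9). The direction is secure for any appreciable correlation; the amount is an assumption. The allocation of both large hospitals to nutrition counselling makes a chance difference in starting BMI worth guarding against. It shows neither that such a difference exists nor that group sizes differ.

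**What to change.** In the Analysis plan, state that exit BMI is compared by randomised counselling package, by intention to treat. Use a linear model adjusted for baseline BMI and home-delivery arm, include the randomisation strata (municipality or the matched pairs), and use cluster-robust standard errors. Align the wording of the endpoint definition with randomised allocation.

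In the Sample size section, give the SD, ICC and, if baseline is used, the baseline–exit correlation behind the BMI figure, and restate the detectable difference to match.

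The cost is a few sentences, with no new measurement and no change to conduct. The wording should be fixed before exit data are examined by counselling package.

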### Sample size

Over the enrolment period, we expect to recruit approximately 700 participants in each of the two trial arms (1,400 participants in total). We calculated the design effect (taking into account clustering of outcomes at the facility-level and varying cluster sizes) for this trial using the ‘clustersampsi’ function in Stata [31]. The design effect was then used to adjust the expected power calculated for a non-inferiority trial under individual randomization, which we determined using the ‘ssi’ function in Stata [32]. Our calculations assumed that 85% of enrolled participants are virally suppressed at baseline as found in a recent cross-sectional study in Dar es Salaam [33]. The margin of non-inferiority was set at nine percentage points. We used a range of intra-cluster correlation coefficients (ICCs) from 0.005 to 0.020. Barnhart et al. calculated ICC values for CD4-cell count measures in Dar es Salaam [34]. The 6-months cumulative incidence for non-adherence to ART (defined as a 50% drop in CD4-count from its peak value and return to pre-ART CD4-count or lower after 168 days on ART or a viral load greater than 10,000 after 168 days on ART) had an ICC value of 0.016 (95% confidence interval: 0.009 to 0.029). We set the probability of a type one statistical error at 0.05 and assumed a correlation coefficient between baseline and endline viral load measurement of 0.5. We find that we are well powered (≥80% power) to detect modest one-sided differences (<9 percentage points) in the proportion of participants who are virally suppressed between the two study arms. Regarding the effect of nutrition counseling on BMI, we are well powered (≥80%) to detect a difference in mean BMI of approximately 1.0 kg/m^2^ or more between the participants in the standard versus the standard plus nutrition counseling arm. This difference is considerably smaller than the difference of 3.1 kg/m^2^ found by Alo et al. between female ART patients randomized to six months of nutrition counseling versus the standard of care in Southeast Nigeria [35]. The trial by Alo et al. is, to the best of our knowledge, the only randomized evaluation to date of the impact of nutrition counseling on BMI in ART patients.

### Data collection

This trial is being implemented by Management and Development for Health (MDH). MDH is a Tanzanian non-governmental organization based in Dar es Salaam, which works closely with Tanzania’s Ministry of Health and Social Welfare. MDH is working on this trial in partnership with the Harvard T.H. Chan School of Public Health, which provides technical assistance throughout the study period.

#### Biomarkers

HIV viral load and hemoglobin are measured at baseline and at the end of the study period. If a participant has had a viral load measurement in the 12 months prior to study enrolment, this measurement will be used as the baseline viral load.

#### Questionnaires

The study’s team of trained data collectors administers a tablet-based questionnaire at enrolment, and then again at the end of the study period. This questionnaire (see Additional file 1) covers self-reported ART adherence, health service utilization, out-of-pocket healthcare expenditures, satisfaction with CHW services, knowledge of HIV, utilization of family planning methods, dietary intake, physical activity, and food production. In addition, the data collectors administer a questionnaire during the enrolment period and during the follow-up period at each participating healthcare facility to a random set of patients after they have accessed an HIV service (i.e., HIV-testing, pre-ART, or ART). This questionnaire (see Additional file 2) asks about patient satisfaction with HIV-related healthcare services, time spent in the facility for the present visit, health service utilization and expenditure, and self-reported ART adherence. Patients for this questionnaire are selected using the sampling method of selecting the next patient entering the consultation [36]. Lastly, a healthcare provider questionnaire is administered to a random set of healthcare workers at each participating healthcare facility during the enrolment period and the follow-up period of the trial. This questionnaire (see Additional file 3) covers job satisfaction, perceived time pressure, and healthcare workers’ views on home delivery of ART.

#### Qualitative data collection

During the enrolment period and at the end of the study period, data collectors trained in qualitative interviewing will conduct semi-structured qualitative interviews with community outreach nurses, CHWs, and participants in the ART home-delivery arm. These interviews aim to ascertain healthcare workers’ and participants’ experiences with ART home delivery, and their suggestions for improvement in the delivery of the intervention. In addition, semi-structured qualitative interviews will be conducted with patients who were offered ART home delivery, but refused to enroll in ART home delivery, to identify their reasoning for preferring facility-based ART.

### Data monitoring

The ability for data monitoring in this trial is limited by the fact that no outcome data is collected on participants during the follow-up period. However, the follow-up period has intentionally been designed to be comparatively short so that in the case of ART home delivery resulting in considerably lower viral load suppression than facility-based care, the adverse effects on patients’ health are relatively minor. We do not expect adverse effects on patients’ health from this intervention given the encouraging results from the trials in Uganda [24] and Kenya [28]. Further, participants in the ART home delivery arm can opt to switch back to facility-based care at any time during the trial period. This trial therefore does not have a data safety and monitoring board.

### Analysis plan

We will analyze the data by intention-to-treat analysis at the patient level in all primary analyses for this trial. The primary endpoint of this trial (i.e., the percentage of participants with a suppressed HIV viral load at the end of the study period) will be assessed by fitting robust clustered log-binomial models. Given the relatively small number of clusters in this trial, we cannot assume that randomization will eliminate confounding despite the matching of clusters described in the study design section. We will, therefore, adjust the analysis for viral load suppression at baseline. As viral load suppression is the outcome variable for the primary endpoint, adjusting for baseline viral load could be considered perfect adjustment for confounders. However, in secondary analyses, we will also adjust for other potentially confounding variables (e.g., participants’ socio-demographic characteristics) as a single baseline measurement may not account for trends in viral load suppression over time. Similarly, in secondary analyses, we will adjust for differing average exposure lengths to ART home delivery at each facility, and conduct subgroup analyses according to whether a participant received ART home delivery and by participants’ exposure length to ART home delivery.

Potential effect modification for any of the endpoints of this trial will be assessed through the likelihood ratio test. If statistically significant effect modification is present, we will present relevant results stratified by the effect modifier. All analyses will be conducted using Stata (Release 13; StataCorp, College Station, TX, USA).

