### Eligibility criteria

The eligibility criteria for participants in this trial are: 1) being aged 18 years or older; 2) attending one of the participating healthcare facilities for ART during the enrolment period; and 3) living in a neighborhood in the facility’s catchment area. An additional eligibility criterion for ART home delivery is being clinically stable on ART. A patient is clinically stable on ART if the patient’s most current viral load has been taken less than 12 months prior to enrolment and showed viral suppression. If a viral load measurement is unavailable at the time of enrolment but a CD4-cell count taken in the 12 months prior to enrolment is available, then a patient is clinically stable on ART if the most current CD4-cell count is >350 cells/μL. If neither a viral load nor a CD4-count taken in the 12 months prior to enrolment is available, then a venous blood sample will be taken for a viral load measurement and the result used for the eligibility assessment. Additional requirements for being stable on ART are 1) taking ART for at least six months, and 2) having had a CD4-cell count >350 cells/μL or a suppressed viral load at six or more months after ART initiation. Patients who are pregnant at the time of enrolment (by patient self-report) or unable to provide written informed consent (e.g., due to mental incapacity) are excluded from eligibility.

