### Study design

#### Rationale for a non-inferiority design and margin of non-inferiority

The non-inferiority design only applies to the primary endpoint (the proportion of participants with a suppressed HIV viral load). This design choice was made because in settings with an existing CHW program, such as in Dar es Salaam, CHW-led home delivery should likely be the standard of care if it does not negatively affect patients’ health outcomes as compared to standard facility-based care. Two virtually certain benefits of CHW-led ART home delivery are a reduction in 1) patient volume at healthcare facilities, which helps to alleviate the severe shortage of skilled healthcare workers in sub-Saharan Africa [20], and 2) the substantial time and financial (e.g., transport costs) burden on patients of having to attend an ART facility [24, 30]. The main drawback of CHW-led ART home delivery is the cost of establishing and running the CHW program, and the risk of overburdening CHWs, which may lead to a reduction in quality and/or quantity of care for non-ART patients. We would argue that in the case of Dar es Salaam, the cost consideration is minor as the CHW program already exists and is likely continue to run independently of whether CHWs are tasked with ART home delivery. Regarding overburdening CHWs, we carefully monitor the number of visits made by CHWs to non-HIV patients in each study arm and also ascertain CHWs’ job satisfaction and perception of the intervention through semi-structured qualitative interviews.

Based on our own judgement of what constitutes non-inferiority for this intervention and in line with the margin of equivalence of nine percentage points used by Jaffar et al. in their randomized trial of ART home delivery in rural Uganda [24], we chose a margin of non-inferiority of nine percentage points.

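### The secondary analyses split participants by receipt and length of home delivery, which are post-randomisation variables with no control counterpart; use a baseline-stable comparison by assigned arm instead

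*Protocol article*

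**What the plan says.** All references are to the Protocol article.

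- **Primary analysis** (Analysis plan): "We will analyze the data by intention-to-treat analysis at the patient level in all primary analyses for this trial". The endpoint is "the proportion of enrolled patients with a suppressed HIV viral load at the end of the study period" (Endpoints), and "The non-inferiority design only applies to the primary endpoint" (Rationale for a non-inferiority design).
- **Secondary analyses** (Analysis plan): "we will adjust for differing average exposure lengths to ART home delivery at each facility"; the team will also "conduct subgroup analyses according to whether a participant received ART home delivery" and by each participant's exposure length.
- **Who can receive delivery** (Eligibility criteria): "An additional eligibility criterion for ART home delivery is being clinically stable on ART". Qualitative data collection foresees refusal of home delivery, and Data monitoring lets participants return to facility care at any time.
- **Exposure** (Endpoints): intervention participants "receive ART at home for a period varying between one and 11 months, and for an average of six months". The article attributes the variation to laboratory delay in those without a recent result.
- **Enrolment** (Enrolment procedure): after checks of stability and of residence in the catchment area, "If both criteria are fulfilled, the data collector conducts the written informed consent procedure".

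**The concern.** Whether, and for how long, a participant gets home delivery is settled after randomisation and only in the intervention arm. No control participant can be classed as a recipient, a non-recipient or a six-month recipient, so the split has no matching control group. Two comparisons are available, and neither is like for like:

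- **Recipients versus all controls** sets a group filtered for stability, willingness and persistence against an unfiltered one.
- **Recipients versus non-recipients** stays inside one arm and has no randomised basis.

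Exposure length is selected too, because it depends on laboratory delay in those lacking a recent result and on staying with home delivery. The planned adjustment for facility-average exposure is related: that average is zero in every control cluster, so it is tied to arm.

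Readers of a non-inferiority trial look to such analyses to learn whether patients who actually got the new care did as well. Here the answer could look reassuring through selection alone.

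**Working it through.** **1. The plan's own figure.** Inputs from Sample size: 700 per arm, 85% suppressed, margin 0.09, ICC 0.005 to 0.020, type one error 0.05 (read as one-sided, since one-sided differences are mentioned). The Abstract gives 24 clusters per arm, so the mean cluster size is m = 700/24 = 29.17. The coefficient of variation (CV) of cluster size is not given and is assumed.

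- DE = 1 + ((1 + CV²) × m − 1) × ICC
- SE = √(2 × 0.85 × 0.15 × DE / n)
- Power = Φ(0.09/SE − 1.645)

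With ICC 0.016 and CV 0.5: DE = 1.567, SE = 0.0239, 0.09/SE = 3.77, power 98%. Over ICC 0.005 to 0.020 and CV 0 to 1, power is 94% to 99.7%. With CV 2.3 (Table 1 patient volumes have CV 2.22) and ICC 0.020 it is 71%, or 81% if the variance is multiplied by 1 − 0.5² for the stated baseline correlation. The stated 80% or more is reproduced.

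**2. Recipients versus all controls, no true effect.** Let s be the stable share, p_s suppression at exit in stable patients and p_u in the rest, equal in both arms. Suppose exactly the stable intervention patients receive delivery. The spurious difference is p_s − [s·p_s + (1 − s)·p_u] = (1 − s)(p_s − p_u). The article gives none of s, p_s or p_u; all are assumptions.

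| s | p_s | p_u | All controls | Recipients − controls | Recipients − non-recipients |
|---|---|---|---|---|---|
| 0.80 | 0.88 | 0.73 | 0.850 | +3.0 points | +15 |
| 0.85 | 0.92 | 0.60 | 0.872 | +4.8 | +32 |
| 0.80 | 0.90 | 0.65 | 0.850 | +5.0 | +25 |
| 0.70 | 0.92 | 0.688 | 0.850 | +7.0 | +23 |
| 0.85 | 0.95 | 0.40 | 0.868 | +8.3 | +55 |

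These are before baseline adjustment. Adjusting for baseline suppression would shrink them. It need not remove them, because the stability rule also uses time on ART and CD4 count, and receipt also depends on willingness and persistence.

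**3. Power of a baseline-stable comparison.** Same formulas with n = 700s per arm over 24 clusters, suppression held at 85%, one-sided 0.05, no baseline adjustment:

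| s | n per arm | ICC 0.016, CV 0.5 | ICC 0.020, CV 1 |
|---|---|---|---|
| 0.8 | 560 | 97% | 92% |
| 0.7 | 490 | 96% | 90% |
| 0.6 | 420 | 94% | 88% |
| 0.5 | 350 | 90% | 85% |

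Example, s = 0.5, ICC 0.016: m = 14.58, DE = 1.276, SE = 0.0305, 2.95 − 1.645 = 1.31, power 90%. At one-sided 0.025 the ranges are 94% to 84% and 86% to 76%.

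**4. Precision of a complier estimate.** With f the share of the intervention arm receiving delivery, the estimate is the intention-to-treat difference divided by f, and its SE is approximately SE/f. Under no effect, power against 9 points on that scale is Φ(0.09f/SE − 1.645). With SE = 0.0239 this gives 91% at f = 0.8, 84% at 0.7 and 59% at 0.5. The share f is not in the article.

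**5. Does the stable set differ from everyone enrolled?** Enrolment procedure takes consent only after stability and residence are both confirmed. Eligibility criteria make stability an extra condition for home delivery alone. Endpoints has home-delivery eligibility assessed once a viral load drawn at enrolment comes back, so an enrolled patient can prove ineligible. Sample size assumes 85% suppressed at baseline, which points the same way, though less firmly because CD4 count can also establish stability. These statements do not fit together.

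**The case against.** The strongest reply is that the article claims little for the receipt split. It is listed as secondary, is nowhere called a support for non-inferiority, and has no named comparator; recipients versus all controls is one reading. The rates in step 2 are assumed and unadjusted, whereas the plan adjusts for baseline suppression. If the Enrolment procedure governs, everyone is stable and that calculation does not arise. All of this stands, and it limits the size of the point. It does not rescue the split: no choice of comparator makes a group formed by receipt comparable by randomisation, and selection on willingness and persistence remains even if all participants are stable.

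A reader might go further and infer that intention-to-treat itself is wrong here because patients who never get home delivery dilute it towards non-inferiority. The documents do not support that. The Abstract and Background define the strategy as home delivery for stable patients together with facility care for the others, and expect less crowded clinics to affect facility patients too. Facility care for unstable patients is therefore part of what is tested, and the 9-point margin was set for all enrolled patients, not for recipients.

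Nor can one infer that no per-protocol or baseline-stable analysis exists. This is a condensed article, and a fuller plan may contain one.

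**Conclusion.** The point holds as a fault in stated secondary analyses. The splits by receipt and exposure length condition on post-randomisation variables found in one arm only, and a better analysis is available from data already planned. The likely direction against all controls favours home delivery. An illustrative size is +3 to +8 points with no true effect, on assumed stable shares of 70% to 85%, assumed suppression rates and no baseline adjustment. That is a range of possibilities and not an estimate of bias in this trial. The primary intention-to-treat analysis is sound for the declared strategy question, and nothing here calls for a second condition for success. How far the baseline-stable set departs from the intention-to-treat set cannot be told until the enrolment statements are reconciled.

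**What to change.** 1. Keep intention-to-treat in all enrolled patients as the sole basis for the non-inferiority conclusion.
2. Replace the receipt split with a comparison by assigned arm among participants who meet the stability rule at baseline in both arms, whether or not delivery was received. Classify from measurements taken at or before enrolment, whenever the result came back. Enrolment procedure and Biomarkers describe these checks without limiting them to one arm. Report it as a risk difference beside the 9-point margin, as supportive evidence.
3. If an effect of actual receipt is wanted, estimate the complier effect with assigned arm as the instrument. State its assumption that assignment acts only through receipt; the expected easing of clinic crowding could breach it, so this too is supportive.
4. Label any remaining receipt, exposure-length or facility-average-exposure analysis as exploratory and non-randomised. Restricting to a minimum time since enrolment does not repair it, because delivery starts after a variable delay.
5. Reconcile Enrolment procedure with Eligibility criteria, Endpoints and Sample size. If only stable patients are enrolled, item 2 coincides with intention-to-treat and item 3 is the useful replacement.

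Cost: wording and one or two extra model runs, with no new data. The stable subset is somewhat less precise (about 85% to 97% power at one-sided 0.05 if 50% to 80% of 700 per arm are stable, with cluster-size CV of 0.5 to 1). The complier estimate loses precision as uptake falls.
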